## Abstract

Supplemental Digital Content is available in the text

## Introduction

1

Functional constipation (FC) is a common functional gastrointestinal disease and one of the most common gastrointestinal diseases of outpatients. The incidence of constipation in the world is about 15%,^[1,2]^ In China, the prevalence rate varied from 6% to 13% from 2010 to 2016,^[3]^ and the prevalence rate of constipation among the elderly in Beijing was 13%.^[3]^ FC does not threaten the life of the patient, but it seriously affects the patient's quality of life (QOL) and causes high medical expenses.^[4]^

Prolonged colonic transit time, pelvic floor muscle dysfunction, and their combined effects are recognized mechanisms for the development of FC. Gender, age, diet, education, and neurological diseases are the main influencing factors of FC.^[5]^ The occurrence of constipation is inversely related to the intake of dietary fiber (fruits, vegetables). A low-fiber diet can induce constipation. The latest diagnosis of FC is based on the criteria of Rome IV Standard, including laborious defecation, dry or lumpy stool, incomplete defecation, anorectal obstruction, prolonged defecation cycle, and manually assisted defecation. Two or more of the above items need to be included with at least 25% frequency for each one. Meanwhile, loose stool is rarely present without laxative and irritable bowel syndrome should be excluded.^[6]^

The treatment of constipation should pay attention to comprehensive management. The routine management of adult functional constipation includes lifestyle intervention, pelvic floor intervention (rectal emptying disorder), and drug treatment. Currently, medical treatment is not satisfactory in continuously improving the symptoms and quality of life of FC patients, and side effects such as electrolyte disturbance, diarrhea, and nausea are often reported.^[7]^ Therefore, it is necessary to find a safe and effective treatment. Reports show that out of 6318 Chinese constipation adults, only 25.1% choose laxatives, and 81.7% of them prefer lifestyle and eating habits as treatment options.^[8]^

Studies have confirmed that the fecal microbiome of FC patients will change, such as the reduction of the number of Preobacterium strains and the decrease of the abundance of microflora.^[9]^ These microbiome changes may be result from low-fiber diet.^[10]^ Different dietary habits, such as low intake of water, fruits and vegetables, and high intake of spicy and greasy foods, all contribute to the increased prevalence of FC. Similarly, increasing the intake of whole fruits can protect the health of the colon and gastrointestinal tract.^[3,11,12]^ The report pointed out that 57% of the intestinal flora depends on the diet structure. Five days of dietary changes may quickly change the human intestinal flora. Therefore, diet is closely related to intestinal flora.^[13]^ Diet can cause constipation by affecting the flora. For example, a lack of isoflavones can cause intestinal flora imbalance, which can lead to constipation.^[12]^ Light vegetarian diet (LVD) is a healthy eating pattern summarized in clinical work. LVD is characterized by vegetarianism, avoiding high-temperature processing, and reducing flavoring.^[14]^

Traditional Chinese medicine formula can effectively improve gastrointestinal symptoms and intestinal health of adults with digestive system diseases. The mechanism is to reduce intestinal permeability, enhance the richness of intestinal flora, and increase the number of probiotics.^[15,16]^ Chinese herbal medicine can improve various chronic diseases, such as coronary heart disease, diabetes, obesity, depression, tumors, etc., by regulating the intestinal flora.^[17]^ Qingjiang Tiaochang Recipe (QJTCF) is a Chinese medicine prescription for treating functional constipation summarized in the clinical practice. The prescription does not contain drugs that can cause melanosis of the colon, such as rhubarb and aloe.

To date, there is no rigorous evidence to support the effectiveness and safety of LVD and QJTCR; thus, this needs authentication based on clinical trials in human subjects. In this protocol, we will design a randomized controlled trial (RCT) to systematically verify that point.

## Methods and design

2

### Study objective and hypotheses

2.1

This exploratory research project aims to study the effectiveness of QJTCF and light vegetarian therapy for functional constipation and the changes of short-chain fatty acids in feces before and after treatment.

### Study design

2.2

The protocol was drafted using the SPIRIT guidelines and the results will be reported following the checklist of the Consolidated Standards of Reporting Trials statement (see Supplementary Table 1). All participants will be informed of the purpose of the study and obtain their informed consent before participating in this parallel group study. According to the inclusion and exclusion criteria, a total of 90 patients with functional constipation are expected to be recruited. Then they were randomly assigned to the Chinese medicine group (group A), placebo + diet group (group B), Chinese medicine + diet group (group C) at the ratio of 1: 1: 1. The patient filled out the case report form (CRF) after confirming enrollment, and the researchers recorded the patient's symptoms, bowel movements, etc., on day 14 (phone follow-up) and day 28. Interventions were provided to subjects based on the enrollment number, but neither the patient nor the investigator knew whether the patient was receiving drug or placebo. The entire study design is shown in the figure (see Fig. 1). A SPIRIT figure for the schedule of enrolment, interventions, and assessments is also presented (see Fig. 2).

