### Sample size

2.5

Because there is still insufficient clinical evidence, this study is a small sample exploratory study with a total sample size of 90 people (each treatment group has 30 samples).

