**Table 3 T3:**
[figure not shown]
The component of Chinese herb powder.

Patients with dietary interventions should follow the above, while patients without dietary interventions will continue their previous dietary habits. The treatment period is 28 days. During the treatment period, record the daily diet and defecation diary. The diet diary will be designed using a semi-quantitative food frequency method, and the defecation diary will collect information about the feeling of defecation, the shape of feces, and the time of each bowel movement. On the 14th day, the patient will be followed up by phone to know the status of the treatment process, and calculate the average number of complete spontaneous bowel movements (CSBMs) per week for the first 14 days, the average score of constipation symptoms and TCM syndrome. After 28 days of treatment, a second follow-up visit will be conducted to understand the condition of constipation (same as the first follow-up visit), and the patient will be required to complete the examination (48 hours gastrointestinal transit Time [GITT], high-resolution anorectal manometry [HRAM], blood routine [BR], liver and kidney function [LKF]). The short-chain fatty acids of the patient 's fresh stool (<30 min) should also be checked and the diary should be retrieved. During the intervention, patients will keep in touch with the researchers. The patient's diet and stool diary will be filled out by the doctor. Keep in touch with each patient in the treatment period through mobile phone software (WeChat), ask the patient to send 3 meals to the doctor's mobile phone, ask the patient about the stool on the day at 7 o’clock every night, and urge patients in the diet intervention group to insist on light vegetarian diet.

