### Randomization, allocation concealment, and partly double-blind

2.8

Third parties not involved in the study will use Excel 2013 software (Microsoft Corporation, Redmond, WA) to generate 90 independent random numbers and divide them by 3. The rest will be 1 in group A, 2 in group A, and 0 in group C. A, B, and C are defined as Chinese medicine group, placebo + diet group, Chinese medicine + diet group. If the enrolled patients fall off, the total number of enrolled patients exceeds 90, and they will be randomly grouped again according to needs. Patient serial numbers will be generated in the order of enrollment. When distributing medicines, neither the doctor nor the patient can know what kind of medicine. The drug number information will be retained, encapsulated, and stored in an opaque envelope, and kept by a third party. When the patient is enrolled, the envelope based on their serial number will be delivered to the researcher. After the trial, the third party will expose blindness. Because dietary intervention is a set of dietary principles rather than specific foods, it is difficult to be blinded, so only drugs are double-blind to reduce information bias.

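### The drug can be double-blind only between groups B and C: in group A the absence of a diet reveals active drug, and the plan has the doctor fill out the stool diary

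*Protocol article*

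**What the plan says.** Section 2.2 (Study design) randomises to "Chinese medicine group (group A), placebo + diet group (group B), Chinese medicine + diet group (group C) at the ratio of 1: 1: 1". Section 2.5 sets 90 patients, 30 per group.

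On blinding, section 2.2 states for all subjects that "neither the patient nor the investigator knew whether the patient was receiving drug or placebo". Section 2.8, whose heading calls the trial partly double-blind, says of the diet that "it is difficult to be blinded, so only drugs are double-blind to reduce information bias". It also says that neither doctor nor patient can know the medicine when it is handed out.

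On diet, section 2.7 (Intervention) says that "patients without dietary interventions will continue their previous dietary habits"; no sham diet is described. The doctor receives each patient's three meals by WeChat, asks about stools every evening, and is to "urge patients in the diet intervention group to insist on light vegetarian diet".

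On recording, section 2.7 says that the patient's "diet and stool diary will be filled out by the doctor". The same section says that the diary is to be retrieved at the 28-day visit. The defecation part covers how the defecation felt, the stool shape and the time of each movement. Section 2.11.2 makes the number of CSBM per week the primary outcome.

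**The concern.** A placebo conceals the drug only if patients who look alike in every other respect could be on either product. Here the diet is visible and placebo exists only alongside it, so knowing a patient's diet status is informative about the drug. Section 2.8 admits that the diet is open but does not follow this through: in one group the open diet also discloses the drug.

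Two things are at stake. First, section 2.2 promises reporting under the Consolidated Standards of Reporting Trials. A report that describes the drug as double-blind throughout would overstate the protection against expectation bias. The Discussion wants to clarify how diet complements the drug. That is C versus A, an open comparison, and the listed limitations do not mention it.

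Second, whether a movement was complete is a subjective report. If the doctor fills out the diary, the person recording it knows diet status for everyone and drug status for group A.

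**Working it through.** No sample-size formula is involved; the check is a conditional probability from the arm definitions.

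**Inputs**
- Group A: active formula, no diet, 30 patients (sections 2.2 and 2.5).
- Group B: placebo, diet, 30 patients.
- Group C: active formula, diet, 30 patients.
- Diet status is open (section 2.8) and is known to the doctor, who sees the meals and urges only the diet patients (section 2.7).

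**The plan's own figure.** 3 × 30 = 90, which agrees with section 2.5.

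**Probability of active drug, given what the doctor knows**
- Diet status unknown: (30 + 30) / 90 = 0.667.
- No diet (A only): 30 / 30 = 1.
- Diet (B and C): 30 / (30 + 30) = 0.5.

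Diet status therefore settles the drug for 30 / 90 = 33% of patients and says nothing about it for the other 60.

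**Pairwise comparisons**
- B versus C: both have the diet and differ only in drug or placebo, with even odds for every patient. It can be drug-blind.
- A versus B: diet differs openly, and the drug is known in A. Open.
- A versus C: diet differs openly. Both groups take the active formula, but the doctor is certain of this in A and has even odds in C. Open.

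**Who draws the inference.** The doctor knows the design, so the inference is certain. A patient must also know that no group receives placebo without diet. The documents do not say how much of the arm structure is disclosed to patients.

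**Source of the primary outcome.** The stool diary is the only described record of individual bowel movements. No sentence says outright that weekly CSBM is counted from it, but no other source is described at that level of detail. Section 2.2 has researchers record bowel movements on days 14 and 28, which raises the same question of who records. Section 2.7 points two ways: completion by the doctor, and retrieval at day 28, which suggests that the patient holds the diary.

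**Assumption.** The remainder rule in section 2.8 sends remainders 1 and 2 both to group A and none to B. Given the 1:1:1 ratio and the group definitions in the next sentence, this is read as a slip and 1:1:1 is used.

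**The case against.** The strongest reply is that most of this is already disclosed. Section 2.8 is headed as partly double-blind and concedes the open diet. Every comparison with A is a diet versus no-diet comparison, so it was open on those terms in any case. The comparison that isolates the formula, B versus C, remains drug-blind. The trial also calls itself small and exploratory, with a larger trial to follow.

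Much of that stands. What the concession does not cover is that section 2.2 makes its statement without exception, and section 2.8 still calls the drugs double-blind. For group A that is a property the design does not have, and neither the exploratory aim nor the condensing of an article explains it.

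Four stronger readings are tempting, but the documents do not support them:
- A reader might infer that group A patients themselves know their drug from the start. That depends on what they are told about the arms, which the text does not say.
- A reader might take the doctor to be unblinded to drug throughout. In B and C the doctor knows the diet, not the drug.
- A reader might infer that the doctor judges or reclassifies completeness. No section says so; how a defecation felt is the patient's report.
- A reader might argue that one misjudged movement a week would reach the response threshold of 1 in section 2.11.2. No misclassification rate is given. CSBM is averaged over weeks, so the error would have to recur. The planned primary test in section 2.14 is a rank test on the number of CSBM, not a test of that threshold.

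**Conclusion.** The concern holds in this form. The unqualified blinding statements in sections 2.2 and 2.8 are wrong for group A, 30 of 90 patients: the doctor can infer active drug with certainty, and patients can too if the three-arm design is disclosed to them. One of the three pairwise comparisons, B versus C, can be drug-blind; the two involving A are open. Separately, section 2.7 gives the diary to the doctor in one sentence and has it retrieved at day 28 in another, and this must be reconciled because the diary appears to feed a subjective primary outcome.

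The conclusion rests on 1:1:1 allocation, on the doctor knowing the design and each patient's diet status, and on weekly CSBM being counted from the diary. The size of any resulting bias in CSBM cannot be estimated from the documents. The point should be corrected, but it does not undermine the B versus C comparison.

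**What to change.** 1. In sections 2.2 and 2.8, restrict the double-blind statement to B versus C, and say that in group A the drug can be inferred from the absence of a diet.
2. Designate C versus B as the drug-blinded test of the formula. Report every comparison with A as open-label.
3. In section 2.7, reconcile who completes the diary. State that the patient records each bowel movement and its completeness directly, and that the doctor may prompt but may not enter or reclassify.

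The first two are changes of wording. The third needs no new arm or extra patients, and the daily WeChat contact is already planned. Its small downside is possibly a few more missing diary entries.

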**Figure 1 F1:**
[figure not shown]
Study design. 48-h GITT = 48-hour gastrointestinal transit time, AEs = adverse events, BR = blood routine, BSFS = Bristol stool form scale, CSBM/W = complete spontaneous bowel movements per week, CSS = constipation-related symptom rating scale, DCR = dietary compliance rate, DQ = diet quality, F-SCFAs = short-chain fatty acids in feces, HRAM = high-resolution anorectal manometry, LKF = liver and kidney function, PAC-QOL = patient assessment of constipation quality of life, PAC-SYM = patient assessment of constipation symptom, TCMSS = traditional Chinese medicine syndrome scale.

**Figure 2 F2:**
[figure not shown]
SPIRIT figure: schedule of enrolment, interventions, and assessments. 48-h GITT = 48-hour gastrointestinal transit time, AEs = adverse events, BR = blood routine, BSFS = Bristol stool form scale, CSBW = complete spontaneous bowel movements per week, CSS = constipation-related symptom rating scale, DCR = dietary compliance rate, DQ = diet quality, F-SCFAs = short-chain fatty acids in feces, HRAM = high-resolution anorectal manometry, LKF = liver and kidney function, PAC-QOL = patient assessment of constipation quality of life, PAC-SYM = patient assessment of constipation symptom, TCMSS = traditional Chinese medicine syndrome scale.

### Exploratory study

2.3

Light vegetarian diet is a new type of dietary model, and QJTCF is a safe and effective prescription. So far, there are no randomized controlled studies on LVD and QJTCF, so this study is an exploratory study. The essence of diet therapy is cognitive behavior therapy. Chinese medicine is complementary and alternative medicine in many countries. Through this research, doctors can pay more attention to the application of cognitive behavioral therapy and traditional Chinese medicine.

### Inclusion criteria, exclusion criteria, and exit criteria

2.4

Participants must meet inclusion criteria (see Table 1) and be excluded from exclusion criteria (see Table 1), while exit criteria (see Table 1) are set for participants who cannot complete the study. Once a patient is included in the trial, the researchers in our team will keep in touch with him or her and try to solve the problems during the treatment to reduce the loss of the intervention. During the trial, patients have the right to withdraw at any condition and will not affect subsequent treatment. The data will be recorded truthfully for further analysis.

**Table 1 T1:**
[figure not shown]
The inclusion criteria, exclusion criteria, and exit criteria for the trial.

### Sample size

2.5

Because there is still insufficient clinical evidence, this study is a small sample exploratory study with a total sample size of 90 people (each treatment group has 30 samples).

### Recruitment

2.6

Participants will be recruited from the outpatients and inpatients of Gastroenterology Department and traditional Chinese medicine (TCM) Gastroenterology Department in China-Japan Friendship Hospital in Beijing through roll-up banners, posters, Wechat, and the hospital official website. Two or more experts (at least 1 from Gastroenterology Department and 1 from TCM Gastroenterology Department) will decide the eligibility unanimously following the inclusion and exclusion criteria. It will be insured that both physicians and patients have no financial interests. All eligible recruiters will sign a written informed consent and those who accept the purpose, benefits, and adverse effects of the study will be enrolled.

### Intervention

2.7

The 2 interventions are light vegetarian diet (see Table 2) and QJTCF (see Table 3). QJTCF (Tongrentang Chinese Medicine) will be made into dry Chinese medicine powder. The placebo will be composed of bitters (Zhejiang Bodanheng Food Ingredients Co, Ltd), caramel color (Guilin Hongxing Food Ingredients Co, Ltd), QJTCF powder and dextrin (Liaoning Dongyuan Pharmaceutical Co, Ltd) with 2: 3: 5: 100 made into brown powder. Use the same type of aluminum foil to pack herbal powder and placebo (12 g per pack). The time for taking Chinese medicine and placebo is half an hour after breakfast and dinner, one sachet at a time, rinsed with warm water.

**Table 2 T2:**

Specific content of light vegetarian food.

**Table 3 T3:**
[figure not shown]
The component of Chinese herb powder.

Patients with dietary interventions should follow the above, while patients without dietary interventions will continue their previous dietary habits. The treatment period is 28 days. During the treatment period, record the daily diet and defecation diary. The diet diary will be designed using a semi-quantitative food frequency method, and the defecation diary will collect information about the feeling of defecation, the shape of feces, and the time of each bowel movement. On the 14th day, the patient will be followed up by phone to know the status of the treatment process, and calculate the average number of complete spontaneous bowel movements (CSBMs) per week for the first 14 days, the average score of constipation symptoms and TCM syndrome. After 28 days of treatment, a second follow-up visit will be conducted to understand the condition of constipation (same as the first follow-up visit), and the patient will be required to complete the examination (48 hours gastrointestinal transit Time [GITT], high-resolution anorectal manometry [HRAM], blood routine [BR], liver and kidney function [LKF]). The short-chain fatty acids of the patient 's fresh stool (<30 min) should also be checked and the diary should be retrieved. During the intervention, patients will keep in touch with the researchers. The patient's diet and stool diary will be filled out by the doctor. Keep in touch with each patient in the treatment period through mobile phone software (WeChat), ask the patient to send 3 meals to the doctor's mobile phone, ask the patient about the stool on the day at 7 o’clock every night, and urge patients in the diet intervention group to insist on light vegetarian diet.

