### Emergency unblinding

2.9

In case of any serious adverse events or emergency, the researcher will report to the supervisor and the main researcher to decide whether to open the emergency letter. Once opened, the case will be treated as exfoliated, excluded from the efficacy analysis, but will remain included in the adverse reaction analysis. Details of the unblinding cause, date, treatment situation, and results will be reported in the CRF and will be signed by the administrator.

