#### Safety outcomes

2.11.4

Safety parameters include AEs and laboratory examinations (BR, LKF).

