### Adverse event

2.12

Adverse events refer to the negative effects caused by the intervention. During the trial, any abnormal reactions of the participants will be reported to the researchers. The time of onset, symptoms, degree, duration, and mitigation measures will be recorded in the CRF.

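### Carry-forward in 2.14 has no exemption for safety laboratory values, and the only scheduled post-baseline BR and LKF come after day 28, so laboratory abnormality rates could be understated for patients who stop early

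*Protocol article*

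**What the plan says.** Section 2.11.4 defines safety in two parts: "Safety parameters include AEs and laboratory examinations (BR, LKF").

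The timing of the laboratory part is in 2.7, in the text after Table 3. Treatment length is fixed ("The treatment period is 28 days"). The interim follow-up is a call: "On the 14th day, the patient will be followed up by phone to know the status of the treatment process". The final follow-up is stated as "After 28 days of treatment, a second follow-up visit will be conducted to understand the condition of constipation", and the examinations required there include "high-resolution anorectal manometry [HRAM], blood routine [BR], liver and kidney function [LKF"]. No other post-baseline BR or LKF appears in the text shown.

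Early exit is foreseen. Section 2.4 refers to exit criteria in Table 1 that "are set for participants who cannot complete the study" and allows withdrawal at any time. Under 2.9, a patient whose code is opened in an emergency is treated as having left the study.

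Section 2.14 says safety indicators will be compared by chi-square or Fisher exact test. It keeps in the analysis every randomised patient with one or more assessments, and a baseline assessment alone is enough. It then applies LOCF to the missing data of dropouts and terminations. It names no variable to which LOCF does not apply.

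**The concern.** LOCF assumes that the last value held can stand for the one not observed. For a safety laboratory test whose only scheduled post-baseline measurement is after day 28, the last value held by an early leaver who was not tested was taken before any exposure. It says nothing about what treatment did. Entered into a chi-square or Fisher table, it counts as an on-treatment result, and usually as a normal one.

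Patients who stop early may include some who stopped because treatment disagreed with them. If so, the untested patients are more likely than the rest to have abnormal results, and the recorded rate is pulled down further. The introduction and discussion present safety as one of the questions the trial addresses. With 30 patients per arm, a few such cases can change the laboratory safety table.

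**Working it through.** The article states no figure on this point, so there is nothing to reproduce. The check is to read the rules together and then illustrate their effect under assumed rates.

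**Reading the rules together**

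1. Scheduled post-baseline BR and LKF: one occasion, after 28 days (2.7). The day-14 contact is by phone, and the nightly WeChat contact concerns meals and stool. Neither yields blood.
2. A patient who stops before day 28 and is not tested has no post-baseline BR or LKF.
3. That patient stays in the analysis set if a baseline assessment exists (2.14).
4. LOCF then applies (2.14). If a baseline BR or LKF was taken, that pre-treatment value is carried. If none was taken, nothing can be carried and the rule does not say what happens. The baseline list in 2.11.1 does not name BR or LKF, so the text alone does not settle which case applies.

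**Illustration A: exit unrelated to the laboratory result**

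Inputs: n = 30 per arm (2.5); assumed true abnormality rate p = 10%; assumed untested early exit d = 5%, 10% or 20%; baseline assumed normal.

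- As observed: n·p·(1−d) / [n·(1−d)] = p = 10% for every d.
- With LOCF: n·p·(1−d) / n = p·(1−d), which is 9.5%, 9.0% and 8.0%.

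Here LOCF introduces an understatement that as-observed reporting would not have.

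**Illustration B: affected patients leave early and untested**

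Inputs: n = 30; p = 10%, so 3 affected patients are expected; f = assumed share of affected patients who leave untested; no other exits; baseline assumed normal.

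- Expected number seen: n·p·(1−f)
- Rate among those tested: n·p·(1−f) / (n − n·p·f)
- Rate after LOCF: n·p·(1−f) / n
- Chance of seeing at least one: 1 − [1 − p·(1−f)]^30

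| f | Seen | Rate among tested | Rate after LOCF | Chance of at least one |
|---|---|---|---|---|
| 0 | 3.0 | 10.0% | 10.0% | 95.8% |
| 25% | 2.25 | 7.7% | 7.5% | 90.4% |
| 50% | 1.5 | 5.3% | 5.0% | 78.5% |
| 75% | 0.75 | 2.7% | 2.5% | 53.2% |
| 100% | 0 | 0% | 0% | 0% |

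For f = 50%: 1.5/28.5 = 5.3%, 1.5/30 = 5.0%, and 1 − 0.95^30 = 78.5%. Going from f = 0 to f = 50%, the chance of seeing at least one falls from 78.5% to 53.2% at p = 5%, and from 99.9% to 95.8% at p = 20%.

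In B most of the loss comes from the missing test, and LOCF adds little to it (5.3% to 5.0%). What LOCF also does is hide the gap, because the table shows 30 results when only 28.5 are expected to exist.

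**The case against.** The strongest reply is that this is a condensed article. The exit criteria (Table 1) and the schedule (Figures 1 and 2, whose legends list AEs, BR and LKF) are not shown, and the full protocol is not at hand. A test at exit may be specified there, and nothing in the text forbids one. This stands: the absence of an exit test is inferred from silence and is not a demonstrated defect.

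A reader might go further and infer that toxicity is measured only in those who tolerated treatment, or that an injury causing an exit would be lost to the trial. The document does not support that. Safety includes adverse events as well as laboratory tests (2.11.4). Section 2.12 covers everyone while on trial: "During the trial, any abnormal reactions of the participants will be reported to the researchers", with onset, severity and duration recorded. Under 2.9 a code-break case is "excluded from the efficacy analysis, but will remain included in the adverse reaction analysis". Patients are also in contact by WeChat throughout treatment. Only the laboratory component is in question. Reported reactions do not wholly replace it, since an abnormality without symptoms would not come to light that way.

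It can also be said that 2.14 states LOCF in general terms and that an analysis plan may treat safety values separately. That is possible. But the rule as written follows directly on the tests named for safety and has no exemption, so it does not depend on the unseen figures. It bites whenever an exit test is missed or declined, even if one is planned.

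**Conclusion.** The point holds in limited form. In the text shown, the only post-baseline BR and LKF follow 28 days of treatment, and the stated LOCF rule covers safety values by default. For an early leaver without a test, any carried value is a pre-treatment one, and laboratory abnormality rates could be understated. The conclusion rests on three conditions: some patients stop early, some of them are not tested, and a baseline BR or LKF exists to be carried. An abnormal baseline value would be carried as abnormal, so the direction is likely but not certain.

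The size cannot be derived from the document, which gives neither an exit rate nor an abnormality rate. The tables above are illustrations. A starker contrast can be built: with two abnormal results among three leavers and one among 27 completers, the recorded rate is 1/27 = 3.7%, or 1/30 = 3.3% after filling, against a true 3/30 = 10%. But it assumes an 18-fold difference in risk between leavers and completers ((2/3) ÷ (1/27) = 18), for which the document offers no basis.

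**What to change.** In 2.14, state that LOCF does not apply to safety laboratory values, that BR and LKF will be summarised as observed, and that the number of patients with no post-baseline result will be reported for each arm. This is a wording change and costs almost nothing. It does not recover missing results, but it stops pre-treatment values being counted as on-treatment ones and lets a reader see how many patients were not tested.

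Separately, confirm whether Table 1, Figure 2 or the full protocol already provides for BR and LKF at early exit. If so, say so in 2.7. If not, bring the planned day-28 BR and LKF forward to the time of exit for patients who stop early and agree. These tests are already planned for every patient, so only their timing changes. The downside is that some who withdraw will decline, as they may, which is why the per-arm count of untested patients is needed in either case.
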